### Recruitment procedure

The recruitment methods of this study follow a previously refined recruitment strategy similar to published protocols conducted within the same laboratory [54, 55]. The primary means of recruitment are targeted advertisements on online interest sites (blogs, parent resource websites, and classifieds) and social media platforms (Facebook, Instagram). For social media posts, the visual and written content are geared toward families. Posts are also targeted to a local parent audience by selecting restrictions for age range, keywords, and interests. A small fee applies these demographic filters and allows the ad to run for about 7 days. Posts are also manually shared to relevant Facebook groups (e.g., parent groups). In addition, posters are regularly placed around the Greater Victoria region at locations such as daycares and preschools, community centres, recreation centres, local coffee shops, and health care centres. Twice a month, a designated Recruitment Officer also offers pamphlets and study information through stalls at family-oriented events such as community markets. In order to ensure a diverse study population, facilities from each region of the city were systematically selected and contacted for recruitment. Recruitment also takes place through word of mouth, whereby current participants refer the study to others by passing on information. Incentives for participation include honoraria at each respective assessment to compensate participants for their time ($25 per family, increasing by $5 increments at each assessment for a total $130 across the study).

Recruitment is rolling across the duration of the study. Families interested in partaking are invited to contact the researchers via email or phone. Upon receipt of inquiries, potential participants are sent additional study details over email and are invited to schedule a phone call. Next, a Recruitment Officer formally screens potential participants over the phone. If they are deemed eligible, they are scheduled for a baseline assessment. Written informed consent is obtained from parents and verbal assent is obtained from children before study enrolment.

### Randomization

Simple randomization is done by the Project Coordinator using computer-generated random numbers in an Excel spreadsheet. Allocation is concealed from the enrolment and assessment team by the Project Coordinator. Upon completion of baseline measures, condition allocation is communicated to the intervention delivery team so as to allow for the correct delivery of materials. Participants are blind to their condition until study completion, at which point they are notified of their allocation by the research team and provided with any additional materials they did not originally receive.

### Procedures and protocol

Once deemed eligible and enrolled, participants are scheduled for a baseline assessment. At this initial meeting, parental consent and child assent are obtained, participating parent(s) are asked to complete a questionnaire, and the research team sends accelerometers home for the participating parent(s) and child (ren) for a week of wear. Upon completion of this objective PA measure, child MVPA is checked against PA guidelines [56] and a secondary screening procedure excludes those families with children meeting guidelines from the trial. Families are then randomized into one of three intervention conditions and a Research Assistant delivers the appropriate intervention. Condition allocation will not require alteration of usual care pathways, and these will continue for all trial arms.

Next, the Project Coordinator schedules all families for “booster” sessions at 6 weeks and 3 months. These sessions involve a house visit by the Research Assistant to discuss any successes, progress, challenges, or setbacks. To encourage adherence to the relevant intervention information, the Research Assistant recaps the relevant intervention materials and facilitates family problem solving based on the family’s experience (see Table 1 for Behaviour Change Techniques per condition). Standardized interviewing techniques are employed [57]. For example, if the Research Assistant learns the family has not been planning their physical activity or employing cues for habit formation, they would discuss how the family may implement these strategies. At these sessions the research assistant also leaves accelerometers and asks the family to complete the online questionnaire at their convenience so long as it is completed within the week.

**Table 1 Tab1:** Description of intervention components and associated behaviour change techniques

Intervention condition	Resources included in booklet	Behaviour change technique label	BCT Number
Education	1. Canadian 24-h Movement Guidelines 2. Benefits of co-activity	Instruction on how to perform a behaviour	4.1
		Information about health consequences	5.1
		Salience of consequences	5.2
		Information about social and environmental consequences	5.3
		Information about emotional consequences	5.6
Planning (+ education)	1. Explanation of goal setting and SMART goal materials 2. Definition of self-monitoring and worksheets for tracking co-activity and outcomes 3. Rationale for planning and co-activity planning worksheets 4. Information on the importance of enjoyment and brainstorming worksheets on fun new co-activities, stimulating environments, and reward structures	Goal setting (behaviour)	1.1
		Problem solving	1.2
		Action planning	1.4
		Self-monitoring of behaviour	2.3
		Self-monitoring of outcome(s) of behaviour	2.4
		Social support (practical)	3.2
		Social support (emotional)	3.3
		Non-specific reward	10.3
		Self-incentive	10.7
		Restructure physical environment	12.1
		Restructure social environment	12.2
Habit (+ education and planning)	1. 1. 1. Habit formation information 2. Examples of habits 3. Cues and anchoring 4. Brainstorming existing routines for tagging co-activity	Prompts/Cues	7.1
		Behavioural practice/rehearsal	8.1
		Habit formation	8.3

*Note.* Behaviour change techniques are coded according to the Behaviour Change Technique Taxonomy Version 1 [58]

Finally, at the six-month mark, accelerometers are left with the family and a final online questionnaire is sent via email. After the week of accelerometer wear, the family is asked to return to the lab for a final meeting and exit interview which qualitatively explores evaluations of the impact of the intervention. Semi-structured interviews are employed to examine both content fidelity and process fidelity of the intervention delivery of the trial.

### Intervention

The interventions are conducted in-person with the family and are delivered by a research assistant. To ensure implementation fidelity, research assistants receive in-depth training on the intervention’s concepts, techniques, and conduct. Interventions for each respective condition involve particular take away materials for the family to employ on their own time. Specifically, a specialized hard-copy physical activity workbook (designed for families and geared towards parents) serves as a template for discussion for all three conditions and is left with the family to fill in and refer to over the course of the study. The Research Assistant explains the concepts and associated worksheets and relays a clear expectation that the workbook is to be completed and used over the course of the study. The workbooks feature colourful imagery and graphic design showcasing family physical activity. The material integrates established Behaviour Change Techniques (BCTs) that are consistent with the M-PAC framework [35]. As per Michie and colleagues’ [58] taxonomy, a complete breakdown of the BCTs employed across conditions is available in Table 1.

The materials are based on previous family-based physical activity interventions targeting self-regulatory processes [34, 59, 60]. Notably, the interventions build upon a recent family physical activity planning randomized trial [34] and advance prior work from a habit formation pilot trial [38]. The habit condition is of key interest. The habit formation condition aims to bring about automatic initiation (or ‘instigation’ [61] of co-activity, such that encountering a cue is sufficient to prompt engagement in co-activity, rather than any available behavioural alternatives, in the absence of any deliberative decision-making process.

### Education condition

The information presented to the education condition includes the Canadian 24 Hour Movement Guidelines, which recommend 180 min of PA at any intensity spread throughout the day with at least 60 min of energetic play [53]. Additionally, facts surrounding the health outcomes of physical activity are provided, including the physical, psychological, social and emotional benefits (BCTs 5.1, 5.2, 5.3, 5.6). An explanation of MVPA and ideas for co-activities are presented with structured and unstructured examples cited (BCT 4.1). Finally, a brainstorming activity is included about potential benefits arising out of co-activity as well as current and possible co-activities.

### Education and planning condition

Those in the planning condition receive all the educational material outlined above (guidelines, benefits, and co-activity ideas/instruction). In addition, the planning condition is presented with various self-regulatory strategies to facilitate problem solving (BCT 1.2) and aid co-activity adoption. Strategies covered include goal setting (how to set SMART goals; BCT 1.1), action planning (explanation and worksheets incorporating where, when, and how to engage in co-activity; BCT 1.4), and self-monitoring (definition and journaling and tracking worksheets to log participation and outcomes; BCT 2.3, 2.4). Furthermore, participants are instructed on the importance of affective attitudes and rewards (BCT 10.3, 10.7) then asked to brainstorm fun new modes of co-activity, enjoyable environments, and potential rewards for being active together, which subsequently allows for the identification of the necessary social and environmental supports (BCT construct 3.2, 3.3, 12.1, 12.2; see Table 1 for complete breakdown of intervention component and BCTs for the planning condition).

### Education, planning, and habit formation condition

The habit formation condition receives the same content as the education condition, plus the regulatory strategies from the planning condition, as well as material on how to develop habits for initiating co-activity. The materials are based on habit formation research [39], informed by a successful pilot study [38], and adapted for families. The habit formation section includes a discussion of what constitutes a habit with non-domain specific examples (night-time routine, morning commute). A fundamental element of the habit section is the idea of utilizing context-dependent repetition (BCT 8.1, 8.3), which includes recommendations on how to nurture repetition during the formation of habits. Namely, a passage on routines and a subsequent brainstorming activity encourages the elicitation of existing routines relevant to the family (e.g., pizza night every Friday). It is explained that tagging PA to these existing routines is an effective way to support repetition. Indeed, this approach has shown efficacy in habit formation in other behavioural domains [62], presumably because it optimizes context-dependent performance by encouraging consistent behavioural patterns, in effect fulfilling the requirements for habit formation. Next, cues (BCT 7.1) are introduced as a factor that prompt behaviour, thereby supporting habit formation. The various forms of habit are then discussed (temporal, social, mood, and visual) with relevant examples. The need for cues to precede the activity and otherwise be rarely present is highlighted. The key to this concept is stimulus-behaviour linkage. For example, a swimsuit bag set by the door to prompt an afternoon family swim might serve as an effective cue as it is highly likely it will activate the behaviour at the opportune moment. Conversely, an ever-present sign by the door would reduce the salience of the cue and in result minimize its potential for activating the desired behaviour. For instance, if one is walking by the door without engaging in activity, there is a theoretical weakening of the link to automatic action over time. It might serve as a reminder for cognitive action, but the cue will not have a strong association if it is not performed with a repeated behavior very often. The next important recommendation is to have consistency in co-activity practices (in the form of protected time for various activities), in order to support instigation habits. Finally, a poster-style summary outlining ten evidence-based tips for translating physical activity intentions into action is provided. The Research Assistant clearly communicates that the workbook should be completed, and the habit formation ideas should be implemented.

### Outcome measures

#### Primary outcome measures

The primary outcome of child MVPA will be assessed with the Actigraph wGT3X-BT Activity Monitor using validated seven-day accelerometry methods for preschoolers. Measurements will take place at baseline, 6 weeks, 3 months, and 6 months (primary endpoint of interest) and MVPA will be evaluated as change from baseline. Currently, the analysis plan is to use the established cut-points and accelerometer best practices outlined below, however the research team recognizes that accelerometer analysis in an ever-changing discipline, therefore we will be responsive to these advances by using the most validated cut-points at the time of study closure. At present, it is anticipated that the MVPA of children will be determined using the cut-points for young children recommended by Janssen and colleagues [63]. These cut-points define moderate to vigorous activity as ≥420 counts per 15 s (≥1680 counts per minute (CPM)). These cut-points have shown fair to excellent validity in preschoolers when compared to direct observation [63].

Children are instructed to wear the device during waking hours for a minimum of 10 h a day for 7 consecutive days (5 weekdays, and 2 weekend days). It is secured by an elastic band and worn around the waist above the right hip. Because the devices are not waterproof, participants are advised to remove them for any water-based activities. In addition, participants are provided with a logbook and parents are asked to note any removals for water activities, record unusual circumstances (e.g., changes to routine such as illness), and make notes with particulars such as structured activity.

To initialize and download the accelerometers as well as analyze the data, ActiLife software version 6.11.9 [64] is used. The devices are initialized to collect data at a 30 Hz sample rate and are downloaded into 15-s epochs in order to capture the sporadic nature of movement in young children and based on common practice for preschooler accelerometry [65, 66]. Data will be included for analysis if children have at least 4 days of valid wear time per week [67–69]. For a day to be considered valid there will need to be a minimum of 300 min (6 h) during waking hours [70]. Non-wear time is defined as ≥20 min of consecutive zero counts or the equivalent of ≥80 consecutive 15-s intervals of zero counts [69, 71]. It is assumed that this non-wear time algorithm captures daytime naps.

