### Tertiary outcome measures

#### Parental physical activity

The tertiary outcome of parental PA is measured both by self-report and seven-day accelerometry at all assessment occasions (baseline, 6 weeks, 3 months and 6 months). Accelerometry will be measured in a similar fashion to the methods outlined above. Namely, parents are instructed to wear the Actigraph wGT3X-BT for 7 days a week for a minimum of 10 h a day, remove it at night and for water-based activities, and note the details of the wear in a logbook. Activity will be assessed by measuring several variables, including duration (total minutes worn, total movement counts/day, total minutes of sedentary, light, moderate-vigorous day), frequency (bouts of sedentary, light moderate-vigorous/day), and intensity. To calculate these variables data will be collected in 10 s intervals and reintegrated into 60 s epochs to align with the methods of Troiano et al., [78]. Non-wear time will be determined using the algorithm from Troiano et al., [78] and will be subtracted from total wear time. As per recommended best practice [79, 80], parents need at least 4 days with 10 h of valid wear per week. Accelerometers have demonstrated reliability and validity when worn for ≥4 days [81–83]. The MVPA of adults will be evaluated as change from baseline and determined using frequently applied cut points [66] validated for adults [78] which classify MVPA as 2020 counts per minutes (CPM) and above. Again, the research team is mindful of the rapidly evolving nature of accelerometry analysis and therefore we will be responsive to the most validated cut-point norms in the field at the time of study closure.

As a secondary self-reported parent PA outcome measure, the Godin Leisure-Time Exercise Questionnaire (GLTEQ), is employed [72, 84] which assesses the frequency and duration of mild, moderate, and strenuous activity performed during free time in a typical week in an open-ended manner. A total weekly MVPA score will be calculated by multiplying the frequency by the duration.

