### Analysis strategy

For each outcome, the pattern of missing data will be evaluated to determine an appropriate analytical strategy [102], after which the normality of all variables will be examined to determine whether transformations will be required. The first set of analyses will make preliminary demographic comparisons among adherers to the study versus dropouts to determine the representativeness of the sample. Next, to address the primary objective (i.e., to determine whether the minutes / day of MVPA change over time similarly for all three conditions, hierarchical linear modeling [103] will be used. Specifically, Level-1 of the model will include an intercept (i.e., the baseline PA) and slope (i.e., to examine potential change over the 4 assessment periods) that will be predicted by Level-2 covariates (i.e., demographics). Additionally, dummy variables will be created for condition (Habit formation group: 1 = yes or 0 = no; Planning group: 1 = yes or 0 = no; Education control: 1 = yes or 0 = No) at Level-2 with the Habit Formation and Planning group variables being added to the model to predict the intercept and slope at Level-1. In doing so, the control group is compared against the other two groups to determine if baseline MVPA is similar across conditions and whether the change in MVPA is similar across conditions. Follow-up analyses will be conducted for the Habit Formation vs. Planning group comparison. To address the secondary objective (i.e., to determine whether the change in the underlying motives explain the potential change in MVPA during the intervention similarly for all 3 groups), a time varying covariate mediation analysis will be used [104]. Briefly, the analyses needed to establish mediation will treat the underlying motives as time varying covariates at Level-1 of the model. Then, the dummy coded condition variables will be entered at Level-2 to determine if the Level-1 motives mediate the condition / MVPA relationship. Finally, to determine whether there is a seasonal, intergenerational, or gender difference across the primary and secondary outcomes (i.e., to address the tertiary objectives), each variable will be entered into the various models at Level-2 to predict the intercepts and slopes at Level-1. Doing so will determine if they impact the change in the various outcomes across time.

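### The cut-point defining the primary outcome is provisional and may be replaced at study closure, with no criterion and no requirement that the choice be blind to results by arm

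*Protocol article*

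**What the plan says.** The primary outcome is child MVPA by accelerometer. Primary outcome measures gives the endpoint and its form: "6 months (primary endpoint of interest) and MVPA will be evaluated as change from baseline". The scoring threshold is provisional: "At present, it is anticipated that the MVPA of children will be determined using the cut-points for young children", with a value of at least 420 counts per 15 s (1680 counts per minute). The same section then says that accelerometer analysis is changing and "therefore we will be responsive to these advances by using the most validated cut-points at the time of study closure".

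Parental physical activity repeats the clause for a tertiary outcome: "we will be responsive to the most validated cut-point norms in the field at the time of study closure".

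Procedures and protocol describes a screening step before randomization: "child MVPA is checked against PA guidelines [56] and a secondary screening procedure excludes those families with children meeting guidelines from the trial". No cut-point is named for that step. The Abstract gives the entry threshold as not meeting 60 minutes of MVPA a day.

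Randomization says that participants are blind and that allocation is concealed from the enrolment and assessment team. It does not say who chooses the final cut-point or whether that person is blind to arm. Research ethics processes and monitoring sends protocol changes to the ethics board and then the registry, without a condition on blinding.

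**The concern.** The cut-point turns accelerometer counts into minutes of MVPA, so a different cut-point gives a different primary endpoint. The article sets the time of the final choice at study closure, after the last outcome data are collected. Even when the article was written, the Discussion reports 44 families with completed 6-month measures. Nothing says how candidate cut-points would be ranked, who would rank them, or that this would happen before results by arm are seen. Nothing commits the team to report the 420-count result if another cut-point is adopted.

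With those safeguards unstated, a reader of the final report could not rule out that the endpoint was picked with the results in view. The article itself states this open rule, so it is not a detail merely left to an analysis plan.

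There is a second, smaller consequence. Children were screened at baseline on accelerometer MVPA with whatever threshold was in use during recruitment. If the closing cut-point differs, the analysed baseline values may not agree with the entry criterion.

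**Working it through.** **The plan's own figure.** There are four 15-s epochs in a minute, so 420 × (60/15) = 420 × 4 = 1680 counts per minute. This matches the article. The provisional definition is internally consistent; the problem is that it is not fixed.

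**What the documents fix and leave open.**

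- Default threshold: given, but as anticipated.
- Time of final choice: study closure.
- Criterion for the best-validated cut-point: none.
- Person who decides: not named.
- Blinding of that decision to arm: not required.
- Retention of the 420-count analysis after a change: not promised.
- Cut-point used for baseline screening: not stated.

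**Size of the risk if the choice were made with arm results known.** The documents give only the 5% alpha (Justification of sample size). Two further inputs are needed, and both are assumptions:

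- k, the number of candidate cut-points;
- r, the correlation between the test statistics they give for the same arm contrast. It should be high, since all candidates score the same recordings.

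Under no true difference, write the k statistics as z_j = √r · c + √(1 − r) · e_j, with c and e_j independent standard normal. The worst case keeps the most favourable one, so the error is P(max |z_j| > 1.96) for one two-sided contrast. Simulated with 400,000 draws:

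| r | k=2 | k=3 | k=5 |
|---|---|---|---|
| 0.80 | 7.7% | 9.8% | 12.7% |
| 0.90 | 7.0% | 8.3% | 10.2% |
| 0.95 | 6.5% | 7.3% | 8.5% |
| 0.98 | 6.0% | 6.4% | 7.2% |

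The ranges are therefore about 6-8%, 6-10% and 7-13%. If the choice is made without knowledge of results by arm, a single test is carried out on a definition chosen independently of the contrast, and the error stays at 5%.

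**Link with entry.** A lower closing threshold counts more epochs as MVPA, so a child admitted as below 60 minutes a day could be re-scored at or above it at baseline. A higher threshold works the other way: some children screened out might have qualified. How many cannot be computed, because neither the screening cut-point nor the distribution of baseline counts is given. Applied alike to all arms and visits, a changed cut-point does not bias the randomized contrast.

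**The case against.** The best case for the plan is that it names a numerical default from established practice and ties any change to advances in the field, not to trial results. Following better methods is a reasonable aim, and the default may well stand. There is also an amendment route through the ethics board and registry. All of this is fair. It means that a change is permitted, not planned, and that nothing in the article shows an intention to choose by result. It does not close the gap: the amendment route has no blinding condition, and the clause could be read as authorising a switch in advance.

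Several stronger readings are tempting, and the documents do not support them:

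- A reader might infer that the cut-point will be chosen afresh by people who have seen the results. The article does not say who decides. Holding the data is not the same as having seen outcomes by arm.
- A reader might assume that 420 counts per 15 s was the screening threshold, so that any change breaks the link with eligibility. The text says only that "child MVPA is checked against PA guidelines". A mismatch is possible, not shown. Participants and eligibility also makes parent-declared activity an entry criterion and treats accelerometry as a second check.
- A reader might add that Analysis strategy leaves the outcome scale open as well, since "the normality of all variables will be examined to determine whether transformations will be required". That is a general preliminary step for all variables. Its detail is commonly left to an analysis plan, and it is a separate matter from the cut-point.

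**Conclusion.** The point holds in this limited form: the primary outcome's cut-point may be replaced after all outcome data exist, with no stated criterion and no required blinding to results by arm. The text of Primary outcome measures is enough to establish that.

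The error rates of roughly 6% to 13% are a worst-case illustration on assumed k and r, conditional on a choice made with arm results known. They are not an estimate of what this trial will do. The possible mismatch with screening concerns who the enrolled children are said to be, and leaves the validity of the comparison between arms intact. The matter should be put right because it touches the primary endpoint and is easily settled before outcomes are seen by arm.

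**What to change.** In Primary outcome measures, replace the open clause with a fixed rule:

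- At least 420 counts per 15 s is the primary definition of child MVPA at baseline and every follow-up visit.
- Any newer cut-point is reported as a named sensitivity analysis.
- If a change to the primary definition is judged necessary, it is made by dated amendment before anyone sees outcomes by arm. Baseline and follow-up are re-scored alike, and the 420-count analysis is kept as a sensitivity analysis.

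In Procedures and protocol, state which cut-point was used for the baseline accelerometer screening. If it differs from the primary definition, report how many enrolled children reach 60 minutes a day at baseline under that definition.

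The cost is a few sentences of protocol text and a re-scoring run on the stored accelerometer data. The one downside is small: the primary analysis may rest on an older cut-point, with newer ones still reported beside it.
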